### Analysis contents

List the frequency of cases enrolled, violated and dropped out;List the details of cases of violation, dropout, low compliance, time-window violation, out of protocol drug usage.List the datasets for analysis.Comparability analysis: compare demographic data and other baseline indicators to measure the balance of each group.Effectiveness analysis: FAS and PPS analysis. The study is a multi-center clinical trial, the influence of central effect on efficacy indicators should be considered in the analysis. Measurement data uses covariance analysis which considering the central factor, and count data uses CMH test corrected by the central stratification.Safety analysis: compare the incidence of AE in each group and describe the AE in the trial. Compare the changes of normal/abnormal laboratory indicators before and after the test, and list the details of cases with abnormal/abnormal aggravation before and after the test.Concomitant medication analysis: compare the details of each group and list them down.

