### Outcomes

By searching for relevant literature [26–28] and interviewing relevant clinical experts, we observed the efficacy from five dimension: temperature, symptoms, use of antipyretic analgesics, etiological test and inflammatory factor test.

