**Indicator check**						
Temperature	√	√	√	√	√	√
BP/HR/P/symptoms/signs	√	√	√	√	√	√
Blood routine/Urine routine	√					√
Liver function/Kidney function	√					√
Twelve-lead ECG	√					√
Pathogen test	√					√
Inflammatory factor test	√					√

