### Statistical method

Data analysis will be performed by professional statisticians using SAS 9.1.3. For measurement data, Group t test or Wilcoxon rank sum test will be used for comparison between groups; for counting data, χ^2^ test and Fisher exact test will be used, Rank sum test and Cochran Mantel Haenszel (CMH)test will used for grade data; for efficacy indicators, PPS analysis and FAS analysis will be used at the same time. The statistical analyses will use the two-sided hypothesis test. P ≤ 0.05 will be set as the significant level.

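### For efficacy measures taken at day 0 and again after treatment, the analysis names centre but not the measure's own day-0 value, which gives away precision on supportive measures

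*Protocol article*

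**What the plan says.** The Outcomes section of the protocol article lists five efficacy dimensions: "temperature, symptoms, use of antipyretic analgesics, etiological test and inflammatory factor test". In Table 2 the row "Inflammatory factor test" is ticked at day 0 and 120 h. The row "BP/HR/P/symptoms/signs" is ticked at day 0 and at 24, 48, 72, 96 and 120 h.

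The analysis of such data is described in two places.

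- Statistical method: "For measurement data, Group t test or Wilcoxon rank sum test will be used for comparison between groups". Graded data are handled separately: "Rank sum test and Cochran Mantel Haenszel (CMH)test will used for grade data".
- Analysis contents, effectiveness item: "Measurement data uses covariance analysis which considering the central factor". The sentence before it gives the reason, namely that the trial is multi-centre. Count data receive a CMH test stratified by centre.

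Baseline values have one stated use, in the comparability item: "compare demographic data and other baseline indicators to measure the balance of each group". No efficacy analysis is said to use them.

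**The concern.** When a measure is taken before and after treatment, part of the spread in the later value is only the spread in where each child started. A two-group t or Wilcoxon test on the later value leaves that spread in the error term, and so does a model with treatment and centre alone. A raw change score does not fully solve this. When the correlation is below 1 it subtracts too much of the starting value, so it stays correlated with baseline.

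The stake is precision on the measures meant to support a claim of anti-inflammatory and symptomatic effect. A chance difference in day-0 values would also pass into the estimate. The plan would display that difference in the balance check, but no stated analysis removes it.

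**Working it through.** **Which outcomes are affected.** Set against the stated methods:

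- Inflammatory factors (0 and 120 h) are the clear case: a before-and-after measure that would ordinarily be continuous.
- A total symptom score is affected only if it is analysed as a continuous measure. The article does not say that it is.
- Under Secondary Outcome measure, the symptom outcomes are time of alleviation, degree of remission and disappearance rate of individual symptoms. A time has no day-0 value of its own, a rate is count data, and a degree of remission may be graded. These can fall under other stated tests.
- The primary outcome, time of temperature recovery, has no day-0 value of its own.

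**The plan's own figure.** The article gives no power figure for these measures. Its only size figure is 100 per group for the primary outcome. It is reproduced if 15.35 h is read as a superiority margin, with two-sided 0.05 and an assumed 80% power:

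- Difference beyond the margin: (46.50 − 30.47) − 15.35 = 16.03 − 15.35 = 0.68 h.
- Pooled SD: √((1.74² + 1.69²)/2) = 1.715.
- n = 2 × 1.715² × (1.960 + 0.842)² / 0.68² ≈ 100 per group.

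Only the 100 per group is carried forward, as a reference size.

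**Inputs for the precision check.** n = 100 per group (article), two-sided 0.05 (article), starting power 80% (assumed), and correlation ρ between the day-0 and later value (assumed, shown as a range). Equal SDs at both times are assumed.

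**Formulas.** With the outcome SD set to 1, the residual variance is:

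- post-treatment value alone: 1
- raw change: 2(1 − ρ)
- adjusted for the day-0 value: 1 − ρ²

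Power after adjustment is Φ(2.802 × k − 1.960). Here k = 1/√(1 − ρ²) against the post value, and k = √(2(1 − ρ)/(1 − ρ²)) = √(2/(1 + ρ)) against the change score. At 100 per group, the difference with 80% power on the post value is 2.802 × √(2/100) = 0.396 SD.

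**Results.** Each power column starts from 80% under its own comparator.

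| ρ (assumed) | 1 − ρ² | Equivalent n per group, 100/(1 − ρ²) | Power against post value | Power against change score |
|---|---|---|---|---|
| 0.1 | 0.99 | 101 | 80.4% | 96.5% |
| 0.3 | 0.91 | 110 | 83.6% | 93.5% |
| 0.5 | 0.75 | 133 | 89.9% | 89.9% |
| 0.7 | 0.51 | 196 | 97.5% | 86.0% |
| 0.8 | 0.36 | 278 | 99.7% | 84.0% |

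Example at ρ = 0.5: k = 1/√0.75 = 1.155, and 2.802 × 1.155 − 1.960 = 1.275, so Φ = 0.899. Example at ρ = 0.8 against change: k = √(2/1.8) = 1.054, and 2.802 × 1.054 − 1.960 = 0.993, so Φ = 0.840.

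**Chance imbalance.** If the groups differ by D at day 0, the expected shift in the estimate is ρD for the post value, (ρ − 1)D for the change score, and 0 after adjustment. At ρ = 0.5 the first two are half of D, in opposite directions.

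**The case against.** The strongest reply is that the article is silent on baseline and does not exclude it. The covariance sentence follows one about centre effects and answers that single issue. It does not set out a full model. A model with treatment and centre alone would usually be called analysis of variance, so the name may even hint at a continuous covariate. A full covariate list may also sit in a statistical analysis plan that is not shown. This stands: a reader might infer that the plan adjusts for centre only, but the text does not say so. It does not remove the point, because the Statistical method section positively names two-group tests that take no covariate. The only use given for baseline values is the balance check.

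A second reply is that the symptom outcomes may already be defined against the starting state, or may be graded, count or time data. This also stands. It limits the point to the inflammatory factors and any score treated as continuous. The inflammatory factors are an efficacy dimension under Outcomes but are missing from the list under Secondary Outcome measure, so their weight is supportive.

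A third reply is that a linear model at every visit would suit symptom scores poorly. Many may reach zero within the five days, and the correlation with baseline may then be low. This is a fair reason not to replace the rank-based tests across the board, and the fix does not.

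A reader might also infer biased results. Randomisation prevents systematic bias; what remains is lost precision and chance imbalance within this one trial. Nor is the gain uniformly large at high correlations: over a change score it shrinks as the correlation rises, to about 4 points at 0.8.

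**Conclusion.** The point holds in a limited form. For measures taken at day 0 and after treatment and analysed as continuous, the article names unadjusted tests and a covariance analysis that considers centre. It names no adjustment for the measure's own day-0 value. Adding that value is a better method than the one stated and uses data already scheduled.

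The size cannot be fixed from the documents, because it depends on a correlation that they do not give, on an assumed starting power of 80%, and on equal SDs at the two times. Across assumed correlations of 0.3 to 0.7, the gain is about 4 to 17 points of power over the post value and about 6 to 13 points over a change score. At 0.1 there is almost no gain over the post value.

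The consequence is confined to supportive measures. The primary analysis, the sample size and the validity of the planned tests are untouched.

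**What to change.** In the effectiveness item of Analysis contents, add a sentence to this effect: continuous efficacy measures recorded at day 0 and after treatment (the inflammatory factors at 120 h, and any total symptom score analysed as continuous) are compared by covariance analysis with treatment, centre and that measure's own day-0 value. Both values are log-transformed if the distribution is skewed. State that, for these measures, this replaces the t or Wilcoxon test in Statistical method, so that one method is fixed before unblinding. Outcomes handled as grade, count or time data keep the tests already named.

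If a fuller analysis plan already includes the day-0 value, the article's wording only needs to be brought into line with it.

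The cost is one sentence. No further patients, visits or samples are needed, and the primary outcome and the total of 240 stay as they are.

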### Sample size estimation and randomization

Taking time of temperature recovery as clinical main efficacy indicator, we calculate two groups’ sample size using mean superiority test formula. According to data of efficacy evaluation about adult influenza treating with RDN and Oseltamivir in the early stage, the per protocol set (PPS) of time of temperature recovery comes: Oseltamivir is 46.50 ± 1.74(h) and RDN is 30.47 ± 1.69(h); so that δ for 15.35 h, 100 participants will be required for each group, and 200 is the total. If the 20% dropout rate is considered, 240 cases were planned to be observed. We adopt the method of center stratified block randomization in trial: there is 10 centers, 4 segments, each center has 24 cases and each group has 12 cases.

Randomization will be used for patient allocation [22]. The randomization will be performed by an independent statistician. The random numbers are divided into two groups sequentially: experimental group and control group. SAS 9.1.3 statistical software will be used for seed number, and randomized grouping tables will be generated for the 240 patients receiving treatment. During the trial, the investigator will be able to obtain the randomized number and drug number of each patient from the designated central randomized platform. All random numbers grouped are sent to each trial center and corresponding treatment kits are provided.

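### The protocol names both centre-ignoring and centre-adjusted tests for the same efficacy data and does not say which is primary

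*Protocol article*

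**What the plan says.** Two sections of the protocol article assign tests by type of data.

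- **Statistical method.** "For measurement data, Group t test or Wilcoxon rank sum test will be used for comparison between groups", and "for counting data, χ^2^ test and Fisher exact test will be used". The same sentence continues "for efficacy indicators, PPS analysis and FAS analysis will be used at the same time". Nothing restricts these tests to baseline or safety data, and no rule decides between t and Wilcoxon.
- **Analysis contents**, effectiveness item. It states that "the influence of central effect on efficacy indicators should be considered in the analysis" and then: "Measurement data uses covariance analysis which considering the central factor, and count data uses CMH test corrected by the central stratification".

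The Sample size estimation and randomization section gives the design: "We adopt the method of center stratified block randomization in trial", with 10 centres, and "each center has 24 cases and each group has 12 cases".

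The primary outcome, time of temperature recovery in hours, is measurement data and so falls under both rules. Negative conversion of the antigen test, disappearance of symptoms and complications are counts, and they also fall under both. Graded data are named only in the Statistical method section, so no conflict arises there. Table 2 schedules temperature at Day 0.

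**The concern.** Each measurement or count outcome has two named analyses that will generally give different p-values and confidence intervals. One uses the factor on which randomisation was stratified and the other does not. Two things are at stake.

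1. **Precision.** Stratification balances the arms within each centre, so differences between centres cancel out of the treatment comparison. An unadjusted test still counts those differences as noise. Its standard error is then too large, its type I error falls below 5%, and power is lost.
2. **A defined primary result.** With no order of precedence, a reader cannot tell from the protocol which p-value for time of temperature recovery decides the trial.

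**Working it through.** **The plan's own figure.** The stated 100 per group reproduces as an unadjusted comparison of two means if 15.35 h is taken as a superiority margin and power is assumed to be 80% (the article does not state it).
- Observed difference: 46.50 − 30.47 = 16.03 h. Distance from the margin: 16.03 − 15.35 = 0.68 h.
- Pooled variance: (1.74² + 1.69²)/2 = 2.942.
- n = 2 × (1.96 + 0.8416)² × 2.942 / 0.68² = 99.9, that is 100 per group.

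This formula has no centre term, so it does not show that the centre-adjusted analysis was the one intended.

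**Size and power with centre ignored.** Let ρ be the share of outcome variance between centres; the documents give no value. With 1:1 balance inside every centre, the true standard error of the difference is √(1−ρ) times the one that the t test uses, approximately. Therefore:
- t test, type I error = P(|Z| > 1.96/√(1−ρ))
- t test, power = Φ[(λ − 1.96)/√(1−ρ)]
- centre-adjusted, power = Φ[λ/√(1−ρ) − 1.96]

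Here λ = d√(n/2). With all 240 children (n = 120 per arm) and an assumed effect d = 0.3625 SD, λ = 0.3625 × √60 = 2.808.

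| ρ | t test, type I error | t test, power | centre-adjusted, power |
|---|---|---|---|
| 0 | 5.0% | 80.2% | 80.2% |
| 0.05 | 4.4% | 80.8% | 82.1% |
| 0.10 | 3.9% | 81.4% | 84.1% |
| 0.20 | 2.8% | 82.8% | 88.1% |

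Simulation agrees. With 10 centres of 20 children, normal data and 20,000 trials per setting, the t test rejected in 4.4%, 4.1% and 3.2% of null trials at ρ = 0.05, 0.10 and 0.20. The Wilcoxon test was similar, and the centre-adjusted model stayed at 4.9-5.2%. At an effect of 0.4 SD (λ = 0.4 × √50 = 2.828), power at ρ = 0.05 was 80.6% (t) and 81.8% (adjusted). At ρ = 0.20 it was 83.5% and 88.1%.

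**Free choice among the named tests, one analysis set.** Taking the smallest p-value of t, Wilcoxon and centre-adjusted model, with ρ from 0 to 0.3, type I error was 5.1-6.0% for normal data and 5.8-7.8% for skewed data. For counts, the smallest of chi-square, Fisher and stratified CMH rejected in at most 5.4%, which is what chi-square alone gave in that setting.

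**Baseline temperature.** Adding a covariate with within-centre correlation r to the outcome multiplies the residual variance by 1 − r². That is a reduction of 4% for r = 0.2 (0.2² = 0.04), 16% for r = 0.4 (0.4² = 0.16) and nothing for r = 0. The documents give no r.

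**The case against.** The best defence is that the two sections can be read without conflict. Statistical method is a general list by data type, which also serves the baseline and safety comparisons. The effectiveness item in Analysis contents is the specific rule for efficacy, and it respects the stratification. This reading is natural and probably what was meant. It stands as a reason to call the harm small. It does not remove the conflict, because the general list goes on to efficacy indicators in the same sentence and no text states precedence.

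A second defence is that ranking analyses is commonly left to the SAP, which is not shown. It may well settle the matter, but it would then have to overrule one of two protocol sections.

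Three stronger readings may tempt a reader, and the documents do not support them.
- **That the test will be picked after unblinding.** No text says so. The Blinding section withholds assignments until the whole process is completed, and Data management requires blind examination and database lock before analysis.
- **That success in either FAS or PPS would count.** The text says "PPS analysis and FAS analysis will be used at the same time", which requires both analyses. It does not say that one of them suffices, so no inflation figure should be built on that.
- **That omitting baseline temperature is an error.** It is a missed gain in precision. The wording names centre and does not exclude other covariates. The inclusion threshold of 38℃ also narrows the range of baseline temperature, which may weaken its correlation with the outcome.

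One caution applies to the proposed remedy. In the simulation with strongly skewed times, at ρ = 0.20, the linear centre model on the raw scale had 75.5% power against 81.7% for the unadjusted Wilcoxon test. The power advantage shown above is over the t test on roughly normal data.

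**Conclusion.** The conflict is real and concerns the primary outcome, but its consequences are modest. Two sections name different tests for the same measurement and count data, and neither has precedence.

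Ignoring centre does not inflate type I error; it lowers it. At an assumed 5-20% of variance between centres, the t test rejects in about 3-4.5% of null trials, and centre adjustment raises power from about 82% to 83-88%. If centres do not differ, adjustment gains nothing. Free choice among the named tests would bring type I error to about 5-8% for measurements, the upper end only with skewed data, and would barely move it for counts.

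The contradiction rests on the text alone. The sizes rest on assumed centre variance, effect size and distribution, because the documents give none of these for children. A clarification is worth making because it is nearly free.

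**What to change.** 1. State that the centre-adjusted analyses in Analysis contents (covariance analysis with centre for measurements, centre-stratified CMH for counts) are the primary efficacy analyses, in the FAS, with PPS supportive.
2. In Statistical method, limit the unadjusted t, Wilcoxon, chi-square and Fisher tests to baseline and safety comparisons, or label them sensitivity analyses.
3. Add baseline temperature as a covariate in the model for time of temperature recovery. State in advance the scale on which the hours are modelled, given the caution about skewed times.

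The cost is wording and a little extra analysis work. Centre is known from randomisation and baseline temperature is already scheduled for every child, so no new data are needed, and no figure in the article changes.

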### Quality control

#### Measures of quality control

Sponsor and researchers will adopt standard operating procedures (SOP) to ensure implementation of quality control and quality assurance systems for clinical trials. We will verify all observations and findings to make sure each conclusion in clinical trial deriving from original data. Meanwhile we will conduct quality control in every stage to acquire reliable and correct data.

#### Training of investigators

Supervisor with each sub-center will conduct clinical trial training for researchers before starting trials. They will know experimental drug’s nature, function, efficacy and safety (including related information before marketing), and any new information about the drug that finding during the trial.

#### Enhancement of compliance of patients

Researchers will conduct informed consent carefully to ensure subjects understand experimental requirements fully and comply to trial. They should know that the sponsor will provide free trial medication, laboratory examination fees and so on.Using dose counting method monitors subjects compliance. Compliance = actual dosage/prescribed dosage × 100%. Good drug compliance: 80 − 120%; poor drug compliance: less than 80% or more than 120%.Researcher should require subjects to bring all drugs when follow-up and record on CRF. Patients with poor efficacy and compliance will strengthen follow-up.

#### Monitoring of clinical trials

The sponsor appoints supervisor. Supervisor will visit trial hospitals on-site regularly to guarantee clinical protocol’s implementation strictly, and check original data to ensure it is identical with CRF.

#### Audit of clinical trials

The drug supervision and administration department and sponsor will entrust inspectors to conduct inspection systematically to ensure the execution of the trial consistent with protocol, and the data reported by the sub-center is identical with CRF or other original records. The audit will be carried out by personnel who is not directly involved in the clinical trial.

## Discussion

Influenza is getting more and more serious these years and early antiviral treatment can maximize clinical benefits [32]. Oseltamivir is the recommended drug for influenza in children [19]. We don’t know whether there are other drugs can play a better role in treatment for influenza in children. So we designed a study to evaluate the efficacy and safety of RDN for influenza in children comparing with Oseltamivir. 240 patients were divided into experimental group and control group in a randomized, double-blinded, double-dummy, parallel control of positive drug, multi-center clinical trial. Furthermore, we would explore the antiviral mechanism of RDN exactly and provide evidence-based medical evidence for clinical rational usage.

There are two limitations in the study. One is that children cannot express their discomfort symptoms well; another is the results of clinical symptom record table might have subjective factors.

## Data Availability

The data will be available when collected.

## Abbreviations

RDN: Reduning injection
ILI: Influenza-like illness
ADR: adverse reaction
AE: adverse event
NS: normal saline
GS: grape sugar
ECG: electrocardiogram
MedDRA: the Medical Dictionary for Regulatory Activities
BP: blood pressure
R: heart rate
P: pulse
CRF: case report form
PPS: per protocol set
ITT: intention to treat
FAS: full analysis sets
SS: safety analysis set
CMH: Cochran Mantel Haenszel
SOP: standard operating procedure
